### Intervention

The intervention involves alterations in how current health care resources are utilized by LTC facilities. Specifically, we will implement a standardized LTC-ED care and referral pathway (Fig. 2), along with targeted INTERACT® (Interventions to Reduce Acute Care Transfers) tools [24]. INTERACT® is a quality improvement program that includes specific tools and pathways designed to improve the identification, evaluation, and communication around changes in LTC resident health status. This program was developed in the United States and the paper-based tools have been adapted for use in Canada. This project will focus specifically on two INTERACT® tools: The Stop-and-Watch Early Warning tool for HCAs and the Change in Condition file cards for nurses [24, 25].

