**Fig. 1 Fig1:**
[figure not shown]
Implementation of a stepped wedge design

By the end of the study, all 38 participating LTC facilities will have received the intervention. However, the order in which facilities receive the intervention will be determined at random [14]. A stepped-wedge design is an ideal design to evaluate an intervention on a population level, where there are implementation resource constraints. This design is also useful where there are ethical or community concerns that all participating sites should eventually get the intervention. As a crossover design, it also controls for confounding and site-level differences because each site is observed before and after the intervention. Therefore, changes within the wider health system over time can be observed, given data is available from multiple pre-intervention and intervention sites at various points in time [15].

The intervention will be implemented at four to five LTC facilities each quarter (every 3 months), with all facilities having implemented the intervention in 30 months. The pre-implementation phase will take place over 1 month. During the pre-implementation phase the researchers contact the participating sites, meet with site leaders and staff, conduct a barriers to implementation assessment, provide the overarching rationale for the implementation program and outline the plan for implementation (i.e., setting an implementation workshop and determining what additional resources are required). Baseline data with the OPTIC tool and chart abstractions will be done prior to the intervention, with implementation occurring over the subsequent 2 months. The intervention will then become an expected standard care practice at the facility, and thus this will be considered the post-implementation phase.

The order of implementation will be randomized using random number generation to reduce bias, where the unit of randomization is the LTC facility. LTC facilities with the same owner-operator will be randomized to the same implementation period, given that these facilities often share staff. Until the pathway is implemented at a LTC facility, facilities will act as controls for the purposes of analysis.

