**Fig. 2 Fig2:**
[figure not shown]
LTC to ED referral pathway

HCAs’ familiarity with LTC residents put them in an ideal position to identify early changes in a resident’s status, using the Stop-and-Watch tool. Once notified by HCAs of a resident’s change in condition, nurses in LTC will be supported in making decisions using the Change in Condition cards and through early communication with the attending LTC or on-call physician. The goal is to support LTC in early identification and onsite management of changes in health status where appropriate, as well as to improve communication between LTC practitioners. Implementation of INTERACT® tools can result in a significant reduction in hospitalization rates for residents in LTC facilities [24, 25].

The LTC-ED care and referral pathway will serve as a resource for LTC facilities, when making management decisions for LTC residents experiencing an acute change. A call center that serves as a single point of contact for care providers, in order to facilitate care discussions and transfers between facilities (i.e., LTC and ED), will be used to link the LTC physician and nurse to an ED physician. The call centre is called RAAPID (Referral, Access, Advice, Placement, Information & Destination). RAAPID will support a discussion between health care providers regarding the best options for further assessment and care (e.g. ED transfer vs. community paramedicine visit) and help to minimize errors that can occur during transitions in care.

The pathway will also help to further optimize the use of community paramedicine by LTC facilities. The community paramedicine program provides primary and urgent health care to patients in the community, including LTC. The community paramedicine program also has procedures in place to provide facilitated transport to and from diagnostic imaging without an associated ED visit. Studies have shown that the provision of community paramedics within LTC significantly reduces transfers to the ED, improved outcomes, and improved resident and family experiences [12, 26–28].

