### Evaluation plan

The evaluation framework will use a mixed-methods approach, where quantitative and qualitative data collection will occur using a concurrent dominant design. Mixed methods research involves collecting, analyzing, and interpreting quantitative and qualitative data in a single study that investigates the same underlying phenomenon [29]. Mixed methods research is useful for studying complex health issues such as motivations, attitudes, perceptions, beliefs, and values that underlie health behaviours within social, economic, organizational, and political contexts that cannot be captured by either quantitative or qualitative designs alone [30]. The primary outcome will be the change in the rate of transfers to ED from LTC facilities. Specifically, we will compare differences in the rate of transfers per 1000 resident days. This will be used to track the effectiveness of the intervention at the LTC sites (i.e., changes in the rate of transfer before and after the intervention). Data on all LTC-ED transfers are currently collected as part of administrative data by Alberta Health Service Analytics. Over the 30-month study period, our current rate of ED transfers would result in over 8000 LTC-ED transfers from patients within the 38 participating Calgary LTC facilities. After we account for the stepped-wedge design effects and plausible levels of over-dispersion, this will provide 80% power to detect a 15% reduction in the rate of LTC-ED transfers (primary outcome) [15, 31–33].

Secondary outcomes, using data obtained from administrative databases, will include the change in the rate of LTC admissions to hospital per 1000 resident days and the proportion of LTC residents cared for in their LTC facilities through community paramedicine post-pathway implementation. Consenting residents will also evaluate community paramedicine and ED care episodes by completing a modified version of the OPTICS (Older Persons Transition in Care Success; see Additional file 1) Success tool, within 2 days of a community paramedic visit or an emergency department visit that did not result in a hospital admission [31]. The OPTICS tool has been used and validated in previous studies [34, 37].

The appropriateness of the pathway triage decision will be assessed using a random

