In conjunction with AHS analytics we have developed an electronic dashboard specifically designed to support the evaluation of this project. The electronic dashboard was developed by AHS analytics in 2015 on the software Tableau. The dashboard captures monthly data on transfers from facilities. Only selected members of the research team can access the dashboard. Members of the project team (i.e., implementation coach) provide each facility with biannual reports of how the facilities are performing. The dashboard captures data on ED visits from each LTC enrolled in the study per 1000 resident days. RAAPID calls to LTC sites, visits to LTC sites by community paramedicine, and hospital admission rates per 1000 resident days for each facility enrolled in the study. This dashboard will be used as an audit-feedback tool for LTC facilities, as the initiative is scaled up and spread across the province. Additional administrative data captured on the dashboard will include transfer volume, ED arrival mode, primary diagnosis, CTAS score, and EMS events.

The major components of this study have been summarized in Fig. 3.

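### The paramedicine outcome is post-implementation only and counted per RAAPID call, so it cannot show whether use rose with the pathway or whether shared services spilled over to control facilities

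*Protocol article*

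**What the plan says.** Under Intervention, the protocol article describes a change in the use of existing services: "The intervention involves alterations in how current health care resources are utilized by LTC facilities". RAAPID is "A call center that serves as a single point of contact for care providers", and it links the LTC physician and nurse to an ED physician. Of community paramedicine it says: "The community paramedicine program provides primary and urgent health care to patients in the community, including LTC". It adds that "The pathway will also help to further optimize the use of community paramedicine by LTC facilities". The Discussion expects use of community paramedicine to go up.

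Under Study design, "Until the pathway is implemented at a LTC facility, facilities will act as controls for the purposes of analysis". One route of cross-site influence is addressed there: "LTC facilities with the same owner-operator will be randomized to the same implementation period, given that these facilities often share staff".

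Under Evaluation plan, one secondary outcome is "the proportion of LTC residents cared for in their LTC facilities through community paramedicine post-pathway implementation". The Quantitative analysis section makes this a descriptive statistic: the number of community paramedic visits to LTC divided by the total number of RAAPID calls from LTC. The primary model there is a negative-binomial mixed model with site random intercepts, a treatment indicator and fixed time effects.

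The Evaluation plan also describes the dashboard: "The dashboard captures monthly data on transfers from facilities". The same paragraph lists RAAPID calls, paramedic visits and hospital admissions for each enrolled facility.

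**The concern.** A stepped-wedge analysis compares crossed-over facilities with those still waiting, and it takes the waiting facilities as unaffected by the others' roll-out. Here the active ingredients are services that work across facilities. Two things could break that assumption. If crossed-over facilities draw more paramedic visits from a fixed supply, waiting facilities may get fewer and send more residents to the ED. In the other direction, RAAPID staff, ED physicians or paramedics who learn the pathway may carry part of it to waiting facilities. The owner-operator rule covers shared LTC staff and does not reach these routes.

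Two things are at stake. One is the reading of the primary rate ratio, which is meant to inform spread to other regions. The other is more basic. Increased paramedicine use is a central step in how the pathway is expected to work, and the outcome chosen to describe it has no control-period value to compare with.

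**Working it through.** **1. What the fixed outcome can show.** Let V be paramedic visits and C be RAAPID calls in a facility-quarter. The planned quantity is V/C, after implementation only.
- If the pathway doubles both, 2V/2C = V/C. The ratio is unchanged although visits per 1000 resident-days have doubled.
- If calls rise faster than visits, the ratio falls although paramedicine use has risen.
- A change in V at facilities not yet crossed over does not enter, because those quarters are outside the outcome.

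This step needs no assumed figure.

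**2. The plan's own power figure.** The Evaluation plan gives 80% power for a 15% reduction with over 8000 transfers in 38 facilities over 30 months. Alpha, the over-dispersion value and the between-site variance are not given, so 80% can be neither reproduced nor refuted. As a plausibility check I assumed two-sided alpha 0.05, equal facility sizes, each facility as its own cluster, one baseline quarter and 9 steps (4 to 5 facilities per quarter), hence 10 quarters and 8000/(38 × 10) ≈ 21 transfers per facility-quarter. Log rates were analysed by generalised least squares with cell variance 1/21 + k, a site random intercept and fixed quarter effects. With between-site variance of 0.04 to 0.25, and 8 or 9 steps over 9 or 10 quarters, power is about 98% to 99% at k = 0 and reaches 80% at k of about 0.05 to 0.07. The stated figure is attainable. With k set to give 80% (between-site variance 0.1), the standard error of the log ratio is 0.058: |ln 0.85|/0.058 = 0.1625/0.058 = 2.80, and Φ(2.80 − 1.96) = 0.80.

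**3. Spillover confined to control cells, same model.** The spillover sizes are assumptions; the documents give none. The true ratio is 0.85. 'Constant' means full size once roll-out starts. 'Growing' means proportional to the share of facilities crossed over.

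| Assumed control spillover | Expected ratio, constant | Expected ratio, growing |
|---|---|---|
| Transfers up 2% | 0.833 | 0.841 |
| Transfers up 5% | 0.810 | 0.829 |
| Transfers up 10% | 0.773 | 0.809 |
| Controls gain 10% of the log effect | 0.864 (power 71%) | 0.857 (power 76%) |
| Controls gain 25% of the log effect | 0.885 (power 56%) | 0.868 (power 69%) |
| Controls gain 50% of the log effect | 0.922 (power 29%) | 0.886 (power 55%) |

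The constant case follows by hand. Displacement: 0.85/1.05 = 0.810. Learning: 0.85 to the power 0.75 = 0.885. The growing case, which fits a mechanism that builds with roll-out, moves the estimate about half as far on the log scale: for 5%, ln(0.829/0.85) = −0.025 against ln(0.810/0.85) = −0.048.

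**4. No true effect, 5% displacement.** Constant: the expected ratio is 1/1.05 = 0.952, and the chance of a significant apparent benefit is Φ(0.0488/0.058 − 1.96) ≈ 13%. Growing: the expected ratio is 0.975, and the chance is Φ(0.0253/0.058 − 1.96) ≈ 6%. Nominal is 2.5%.

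**5. A shock that reaches all facilities equally in a quarter.** Adding the same term to treated and control cells leaves the estimate at 0.85. The fixed time effects absorb it.

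**The case against.** The strongest reply is that the mechanism is inferred. No passage gives a capacity limit, a waiting time or priority for crossed-over facilities. Paramedicine serves the wider community, so extra LTC demand need not fall on waiting LTC facilities. The text does not say that waiting facilities already use RAAPID in this way. The INTERACT tools, education, champions and coaching are delivered facility by facility and would not travel with a paramedic or an ED physician. All of this stands. A reader might infer that the trial will overstate its benefit because control residents lose paramedic access; the documents do not support that. The two mechanisms also oppose each other, so even the net direction is unknown.

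A second reply is that spillover would not go unnoticed. The dashboard holds the relevant counts for every enrolled facility, and the cost analysis compares costs with and without the program and includes paramedic costs. That also stands, so it would be wrong to say the problem is hidden. What is missing is a stated analysis of control-period visits and calls. Total cost mixes many services and does not isolate them.

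A third reply is that a spillover check belongs in the statistical analysis plan, which is not shown. This is fair for the check taken alone. It does not cover the outcome definition, which the article itself fixes as post-implementation and per RAAPID call. The general sentence on mixed models for other outcomes does not rescue it, because the next paragraph assigns this outcome to descriptive statistics.

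**Conclusion.** The point holds in two parts of different strength. The first follows from the text alone: the paramedicine outcome as defined cannot show whether use rose with the pathway, or whether it changed at facilities still acting as controls, although data for both are already collected.

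The second is conditional. Because the services are not stated to be limited to crossed-over facilities, and only shared staff under one owner-operator is guarded against, spillover is plausible. It would bias the primary ratio away from 1 under control-only displacement and toward 1 under contamination. An equal shock across sites does no harm. The range of 0.809 to 0.886 in the growing case, around a true 0.85, rests wholly on assumed spillover of up to a 10% rise in control transfers or a 50% share of the log effect. It also rests on the assumed alpha, over-dispersion, between-site variance and equal facility sizes. It shows sensitivity and is not an estimate of bias in this trial.

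**What to change.** Define community paramedic visits and RAAPID calls, each per 1000 resident-days, as secondary outcomes in both control and intervention facility-quarters. Analyse them with the same stepped-wedge mixed model as the primary outcome. The visits-per-call ratio can stay as an additional description.

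For control quarters only, display paramedic visits, RAAPID calls and ED transfers against the number of facilities already crossed over. State in advance that this display is a descriptive supporting check. Roll-out only increases with calendar time and overlaps the pandemic, so a trend in it cannot be attributed to spillover alone. For that reason, attach no rule that automatically relabels the primary result, and do not offer a before-after contrast across the 38 facilities as an alternative estimate; that would bring back the time confounding the design is meant to control.

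The cost is a small amount of extra analysis of data already held. The randomisation, the pathway and the primary model are unchanged.

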**Fig. 2 Fig2:**
[figure not shown]
LTC to ED referral pathway

HCAs’ familiarity with LTC residents put them in an ideal position to identify early changes in a resident’s status, using the Stop-and-Watch tool. Once notified by HCAs of a resident’s change in condition, nurses in LTC will be supported in making decisions using the Change in Condition cards and through early communication with the attending LTC or on-call physician. The goal is to support LTC in early identification and onsite management of changes in health status where appropriate, as well as to improve communication between LTC practitioners. Implementation of INTERACT® tools can result in a significant reduction in hospitalization rates for residents in LTC facilities [24, 25].

The LTC-ED care and referral pathway will serve as a resource for LTC facilities, when making management decisions for LTC residents experiencing an acute change. A call center that serves as a single point of contact for care providers, in order to facilitate care discussions and transfers between facilities (i.e., LTC and ED), will be used to link the LTC physician and nurse to an ED physician. The call centre is called RAAPID (Referral, Access, Advice, Placement, Information & Destination). RAAPID will support a discussion between health care providers regarding the best options for further assessment and care (e.g. ED transfer vs. community paramedicine visit) and help to minimize errors that can occur during transitions in care.

The pathway will also help to further optimize the use of community paramedicine by LTC facilities. The community paramedicine program provides primary and urgent health care to patients in the community, including LTC. The community paramedicine program also has procedures in place to provide facilitated transport to and from diagnostic imaging without an associated ED visit. Studies have shown that the provision of community paramedics within LTC significantly reduces transfers to the ED, improved outcomes, and improved resident and family experiences [12, 26–28].

Our evaluation of this change initiative will consider all six dimensions of quality outlined by the Alberta Quality Matrix for Health. Specifically, this evaluation will include an assessment of the impact on LTC-ED transfers, resident/family, health care provider experience, and health care system costs. A data visualization dashboard utilizing Tableau software and designed in partnership with AHS Clinical Analytics will capture facility specific administrative data on transfers. This audit feedback tool will be used as a control for sites to compare the rate of transfers before and after implementation. This data will be provided to the LTC facilities as part of semiannual audit-feedback reports.

### Evaluation plan

The evaluation framework will use a mixed-methods approach, where quantitative and qualitative data collection will occur using a concurrent dominant design. Mixed methods research involves collecting, analyzing, and interpreting quantitative and qualitative data in a single study that investigates the same underlying phenomenon [29]. Mixed methods research is useful for studying complex health issues such as motivations, attitudes, perceptions, beliefs, and values that underlie health behaviours within social, economic, organizational, and political contexts that cannot be captured by either quantitative or qualitative designs alone [30]. The primary outcome will be the change in the rate of transfers to ED from LTC facilities. Specifically, we will compare differences in the rate of transfers per 1000 resident days. This will be used to track the effectiveness of the intervention at the LTC sites (i.e., changes in the rate of transfer before and after the intervention). Data on all LTC-ED transfers are currently collected as part of administrative data by Alberta Health Service Analytics. Over the 30-month study period, our current rate of ED transfers would result in over 8000 LTC-ED transfers from patients within the 38 participating Calgary LTC facilities. After we account for the stepped-wedge design effects and plausible levels of over-dispersion, this will provide 80% power to detect a 15% reduction in the rate of LTC-ED transfers (primary outcome) [15, 31–33].

Secondary outcomes, using data obtained from administrative databases, will include the change in the rate of LTC admissions to hospital per 1000 resident days and the proportion of LTC residents cared for in their LTC facilities through community paramedicine post-pathway implementation. Consenting residents will also evaluate community paramedicine and ED care episodes by completing a modified version of the OPTICS (Older Persons Transition in Care Success; see Additional file 1) Success tool, within 2 days of a community paramedic visit or an emergency department visit that did not result in a hospital admission [31]. The OPTICS tool has been used and validated in previous studies [34, 37].

The appropriateness of the pathway triage decision will be assessed using a random

sample of up to 50 ED transfers and 50 community paramedicine visits. A standardized data collection form will be used by trained abstractors to extract key elements related to these episodes of care from medical records of consenting patients. A panel of physicians, including emergency physicians, geriatricians and physicians working within LTC, will review these completed abstraction forms to determine appropriateness of the triage decision, using the definitions of unnecessary and avoidable transitions developed in the EXACT (Examining Aged Care Transitions) study. This definition was developed through focus groups and interviews with LTC, EMS (emergency medical services) and ED staff and physicians, and then validated through a larger survey [35]. Additionally, the panel will determine if the treatment plan was concordant with residents’ wishes for treatment and goals of care designation.

Safety reviews of medical records will also be completed for up to 50 consenting patients who are treated by community paramedicine and subsequently transferred to ED within 72 h. A standardized form will be used by trained abstractors to extract key elements related to these episodes of care from medical records. These completed abstraction forms will then be reviewed by the physician panel. Specifically, we will use a previously developed six-point scale to determine the degree to which the ED transfer was the result of suboptimal care provided by community paramedicine [36].

Assessing the economic feasibility of this program is important to informing its scale and spread. A comparative cost-analysis will be undertaken, which includes hospitalizations, ED visits, ambulatory care, urgent care center, and physician and paramedic costs. This resource use is routinely captured by administrative data sets. Patient-level cost data will be provided by administrative data collected by the AHS. We will capture physician costs, hospital costs, as well as the cost of implementing our program.

To better explore if and why our intervention is effective, accessible, acceptable, and appropriate, we will conduct interviews and focus groups with patients and/or substitute decision-makers, families, and health care providers. A sample of consenting residents and/or family members will be interviewed using semi-structured interviews. We will interview a mix of residents transferred to ED and treated in LTC by community paramedics. Interviews were chosen in order to best accommodate for mild cognitive impairment and/or sensory impairment among participating residents. The interview questions were developed in consultation with resident and family advisors. The interviews will be 20–30 min in length to allow for an in-depth evaluation, without being too taxing for frail residents. Each interview will be recorded and transcribed verbatim, except for the exclusion of identifying information. Interviews will continue until there is saturation of themes, but it is expected that 15–30 interviews will be required in total [37, 38]. Qualitative data will be analyzed using thematic analysis and the software NVivo [39].

We will also conduct six semi-structured focus groups in total with involved health care providers, (i.e., with ED and LTC physicians, with LTC nurses and HCAs, with RAAPID staff and with community paramedics), in order to determine their experiences with the new LTC-ED care and referral pathway and early detection tools. Focus groups will facilitate a space in which participants are able to share their experiences and inform understandings of facilitators and barriers. Each focus group will last 60–90 min and include 6–12 participants. Focus groups will be recorded and transcribed verbatim, except for the exclusion of identifying information. Residents and/or family members and health practitioners will be interviewed separately.

In conjunction with AHS analytics we have developed an electronic dashboard specifically designed to support the evaluation of this project. The electronic dashboard was developed by AHS analytics in 2015 on the software Tableau. The dashboard captures monthly data on transfers from facilities. Only selected members of the research team can access the dashboard. Members of the project team (i.e., implementation coach) provide each facility with biannual reports of how the facilities are performing. The dashboard captures data on ED visits from each LTC enrolled in the study per 1000 resident days. RAAPID calls to LTC sites, visits to LTC sites by community paramedicine, and hospital admission rates per 1000 resident days for each facility enrolled in the study. This dashboard will be used as an audit-feedback tool for LTC facilities, as the initiative is scaled up and spread across the province. Additional administrative data captured on the dashboard will include transfer volume, ED arrival mode, primary diagnosis, CTAS score, and EMS events.

The major components of this study have been summarized in Fig. 3.

